## Outcomes

5

The study will report on the following feasibility outcome measures to address the research questions for the trial:i)Recruitment, retention, acceptability1.Recruitment rates, assessed as the number of participants eligible, consenting and randomised, out of those screened.2.Reasons for ineligibility/non-participation/non-consent of participants where provided.3.Retention in the study, assessed as the number of participants randomised who are successfully followed up at four and seven months post randomisation with details of withdrawals and loss to follow-up where available.4.Qualitative feedback from research staff, health facility staff and trial participants on trial processesii)Intervention Delivery1.Retention in intervention reported as the total number of sessions attended out of the total number of sessions offered.2.Review of participant session records held by TDAs3.Qualitative feedback from TDAs, mental health facility staff and trial participants on delivery, implementation and receipt of the SCIMITAR-SA intervention.iii)Data completion1.Completeness of data for baseline assessments, outcome measures for the definitive trial and data on health resource use at four and seven months.2.Data completeness of self-reported and biochemically verified continuous abstinence from all tobacco products at seven months.

### Sample size

5.1

The trial will recruit 100 participants across the six facilities (10 from the two Karachi facilities and 20 from the remaining four) which will allow estimation of recruitment (50%) and retention (80%) to within a 7% and 8% margin of error.

### Statistical analysis

5.2

No formal statistical comparisons will be undertaken. Continuous variables will be summarised using means and standard deviations, or medians and interquartile ranges where data are skewed, while categorical variables will be reported as frequencies and percentages. A CONSORT [51] flow diagram will illustrate participant progression through screening, recruitment, intervention delivery and follow-up. The numbers screened, eligible, consenting, and recruited will be summarised, including reasons for ineligibility or non-consent where available. For intervention participants, session attendance will be reported, and recruitment and retention rates by trial arm will be presented with 95% confidence intervals(CIs). Data completion rates for each outcome measure will be summarised by trial arm at baseline and follow-up, along with reasons for withdrawal and any reported adverse events. All analyses will be conducted using Stata (version to be confirmed).

### Process evaluation

5.3

A qualitative process evaluation will be embedded within the feasibility trial to examine (1) the feasibility of trial processes and (2) the delivery of the SCIMITAR-SA intervention and VBA, with a focus on barriers and enablers to implementation within mental-health settings and on providing cessation support to dual users, a novel component of the intervention.

### Feasibility of trial processes

5.4

Research teams in each country will meet at key stages, i.e., after recruitment, intervention delivery, and follow-up, to reflect on procedures including participant invitation (including reports of cessation advice from referring clinician), consent, intervention delivery, data collection, reimbursement, and retention. Meetings will be audio-recorded, summarised, and later reviewed collectively across countries to identify barriers and enablers and agree process improvements. Feedback from mental-health staff involved in identifying or referring individuals with SMI for the trial will also be explored through interviews. In addition, a subset of dual-user participants will be asked about their experience of recruitment, consent, scheduling, and data-collection procedures during follow-up interviews.

### Delivery of the SCIMITAR-SA intervention

5.5

Following completion of intervention delivery, fidelity will be examined using participant session records completed by the TDAs (supplementary file 1). The TDAs will then participate in focus group discussions (six in total) to explore experiences of delivery including fidelity to the intervention protocol, supporting dual users, training and supervision, practical challenges in outpatient settings, and administrative issues such as session scheduling and travel reimbursements. Additionally, 6–12 mental-health staff involved in patient referral, VBA delivery, or trial oversight will be interviewed to gather feedback on integration of the intervention within routine services including potential spillover of behavioural techniques into VBA. We will assess the extent and nature of contamination to refine the methods for the definitive trial and to implement any necessary mitigation strategies. A purposive sub-sample of intervention-arm participants who are dual users (approximately 12, two per site) will be interviewed at the four-month follow-up regarding acceptability and feasibility of the intervention; caregivers may join interviews if participants wish.

All interviews and focus groups will be conducted in local languages at study sites, guided by structured topic guides, and audio-recorded with prior informed consent. Interviews will last up to 30 min and focus groups 60–90 min. The recordings will be transcribed, translated into English, and analysed using the Framework Approach [52] to address applied implementation questions. Microsoft Excel will be used to support data management and analysis.

### Economic analysis

5.6

The economic analysis will involve a preliminary assessment of healthcare resource use and intervention costs from the national health system perspective. Costs of delivering SCIMITAR-SA will be estimated by identifying resources required for set-up, training, supervision, and delivery, including staff time, materials, nicotine replacement therapy (where applicable), communication costs, information sheets, client record materials, and overheads. Comparator costs will include only those related to delivering VBA, typically lasting up to 1 min [53]. Healthcare utilisation data will be collected at baseline and follow-up using self-reported service-use questionnaires, which will be refined based on feasibility findings. During the feasibility stage, patient-level cost profiles and full cost-effectiveness analyses will not be conducted due to limited sample size; instead, intervention costs, healthcare utilisation, and EQ-5D-5L [43] outcomes will be summarised descriptively by trial arm. The analysis will assess the practicality of collecting comprehensive economic and quality of life data and the feasibility of conducting a full economic evaluation alongside a definitive trial.

### Data management

5.7

Two secure REDCap databases will be maintained for the feasibility trial, by ARK Foundation (Bangladesh and Pakistan) and NIMHANS (India). Data managers at each site will perform standardised quality checks, and only authorised personnel (principal investigators, country investigators, coordinators, and research fellows) will have access to identifiable data, held securely at the respective country site and used solely to facilitate participant follow-up. Prior to analysis all data will be anonymised, identified only using unique study IDs.Electronic data will be captured via an encrypted REDCap mobile app [54], stored on secure servers at ARK and NIMHANS, and shared with the University of York for analysis via secure Drop-off services. Qualitative recordings and transcripts will be anonymised, stored in password-protected folders, and erased from recorders after transcription. Separate encrypted files linking personal identifiers with study IDs will be securely maintained. The ARK team will develop a recruitment dashboard and ensure data integrity, preventing duplication or loss. If a participant withdraws consent, only identifiable data will be deleted, while anonymised study data will be retained. All sites will comply with General Data Protection Regulation(GDPR) [55], the UK Data Protection Act (2018) [36], and any local regulations of partner countries. Study materials, including consent forms, screening logs, and anonymised transcripts, will be accessible only to authorised researchers or monitors. At trial completion, anonymised datasets will be archived by the University of York for at least 10 years in line with UK Good Clinical Practice (GCP) guidelines [56] before secure destruction. Hard-copy study documents at all sites, coordinating centres, and the University of York will be stored in locked, secure locations during and after the trial.

### Trial data quality and ethical considerations

5.8

Data quality will be maintained through standardised procedures and oversight by data managers at ARK Foundation and NIMHANS, with additional verification by statisticians at ARK and the University of York. Study data will be securely captured on REDCap servers, de-identified, and password-protected, with restricted editing rights. Automated audit trails will record all data changes, and final datasets will be validated, cleaned, and locked before analysis. Summary reports will be shared periodically with the Independent Advisory Board (IAB).

The SCIMITAR-SA feasibility trial involves individuals with SMI, caregivers, and healthcare staff, and will include sensitive health data sharing across countries. Key ethical considerations include informed consent, data confidentiality, participant vulnerability, and equitable engagement. Participation will require demonstrated capacity to consent, with the right to withdraw at any time. The intervention is low-risk and participant burden will be minimised. Community contributors will be appropriately recognised per NIHR guidance. Ethical oversight will be provided by the Programme Management Group and IAB, with data handled under ARK and University of York governance policies. Staff and participant safety will be ensured through site-specific risk assessments and safeguarding procedures, and participant materials will include independent ethics contact details.

### Adverse events

5.9

Adverse events (AEs) and serious adverse events (SAEs) will be identified, recorded, and reported in accordance with the ICH-GCP [57,58] and national regulations. Although SCIMITAR-SA is a behavioural intervention with minimal anticipated risks, potential AEs include psychological distress during data collection, NRT side effects, and exacerbation of existing mental illness. Participants will be informed about possible side effects and encouraged to report any AEs via study contacts. RAs will assess AEs during counselling sessions and at four- and seven-month follow-ups using standardised checklists and case report forms. Suicidal ideation or self-harm risk will be managed using a suicide-risk pathway adapted from the DiaDeM research programme [59], with immediate referral to designated mental-health professionals. In the event of an exacerbation of mental illness or the occurrence of adverse effects related to NRT, participants will be referred for consultation with their treating psychiatrist. Each AE will be assessed for seriousness, severity, causality, and expectedness. Serious or unexpected events related to the intervention will be reported within 24 h to country leads and within seven days to the University of York, which will coordinate onward reporting to ethics and regulatory authorities. All events will be followed to resolution. Safety data will be summarised descriptively, with all AEs and SAEs promptly reported. Annual safety reports and urgent safety measures will be managed by the sponsor (University of York) in collaboration with country leads.

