### Details of interventions

2.4

The details of each are given below. All participants with SMI will receive usual care, including Very Brief Advice (VBA) and a self-help educational leaflet. Participants allocated to the intervention arm will, in addition, receive the SCIMITAR-SA intervention.

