### SCIMITAR-SA intervention

2.6

SCIMITAR-SA intervention consists of up to seven individual counselling sessions (20–30 min each) delivered over approximately six to seven weeks by trained Tobacco Dependence Advisors (TDAs) experienced in caring for mental health patients (specialist or non-specialist) who receive specific SCIMITAR-SA training and supervision. The intervention will allow for two pre-quit sessions, a quit day session (corresponding with 30 days since enrollment) and weekly follow up to the 4-week post-quit point. In line with the findings of SCIMITAR-UK [35], the sessions may be adapted into shorter, more frequent contacts, with duration extending beyond 6-7 weeks as needed. A model of trainer-of-trainers (ToT) will supervise and support TDAs, with both groups receiving comprehensive training and follow-up discussion from behaviour change experts.

Sessions will be delivered face-to-face up to the quit day, with the option of remote delivery (phone or WhatsApp) if in-person meetings are not feasible. The intervention adopts a participant-centred approach, helping participants articulate reasons for quitting, identify triggers, and develop coping strategies. The TDAs will provide tailored information, reinforce progress, and review challenges throughout the quit journey. Caregivers may assist with logistics but will not participate in counselling sessions. Participants will receive reimbursement for their travel and time for research purposes (BDT 1000/INR 500/PKR 1500 per visit).

SCIMITAR-SA is a behavioural programme; cessation aids such as nicotine replacement therapy (NRT) are not provided but may be used if available through usual care. When participants choose to use NRT, TDAs will advise on appropriate type, dosage (quantity and strength), and potential side effects, with details recorded in case report forms at follow-up assessments (see Fig. 1).

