## Baseline and follow-up data collection procedures

4

After recruitment, data will be collected from participants, with or without the support of caregivers, at baseline (after informed consent and prior to randomisation) and at four and seven months post-randomisation. The trained RAs will administer all instruments in person using REDCap [36] on electronic tablets. Participants in the intervention arm will have a 30-day grace period to set their first quit date, and all follow-up assessments will take place at four and seven months after randomisation.

The information collected at each follow-up, is summarised in Table 1.

**Table 1 tbl1:** Baseline and follow-up data collection procedures.

	Measurement/data collection	Baseline	4 month follow-up	7 month follow-up
1	Socio-demographic and household information	X		
2	History of tobacco use and attempts to quit	X		
3	Quick SCID (module A and B only)	X		
4	Brief Psychiatric Rating Scale (BPRS)	X		X
5	Self-reported abstinence from tobacco products (past 7-days and since quit date)		X	X
6	Salivary cotinine and anabasine (for biochemical verification)			X
7	Nicotine dependence and urge to use tobacco	X	X	X
8	Quitting intentions, motivations and behaviour	X		
9	Health-related quality of life	X	X	X
10	Mental and physical health	X	X	X
11	Health service utilisation	X	X	X
12	Physical measurements – height and weight, waist circumference Vital signs (Blood pressure, heart rate)	X	X	X
13	Researcher meetings to discuss trial processes	X	X	X
14	Interviews with mental health staff and managers to discuss trial processes and SCIMITAR-SA implementation		X	
15	Focus group discussions with TDAs to discuss SCIMITAR-SA delivery, implementation and administration		x	
16	Interviews with dual users to gather feedback on trial processes and the SCIMITAR-SA intervention		X	
17	Participant session records held by TDAs		X	

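### Adverse events are also elicited at counselling sessions that only the intervention arm attends, so a pooled by-arm summary may inflate its non-serious event counts

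*Protocol article*

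**What the plan says.** Section 5.9 (Adverse events) sets the ascertainment schedule: "RAs will assess AEs during counselling sessions and at four- and seven-month follow-ups using standardised checklists and case report forms". It also gives a passive route, open to both arms: "Participants will be informed about possible side effects and encouraged to report any AEs via study contacts".

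Section 2.4 fixes who has sessions. Everyone gets the same background care ("All participants with SMI will receive usual care, including Very Brief Advice (VBA) and a self-help educational leaflet"), and "Participants allocated to the intervention arm will, in addition, receive the SCIMITAR-SA intervention". Section 2.6 gives the number and timing: "SCIMITAR-SA intervention consists of up to seven individual counselling sessions (20–30 min each) delivered over approximately six to seven weeks". Section 4 gives the contacts shared by the arms: "all follow-up assessments will take place at four and seven months after randomisation". Table 1 lists no data collection from control participants between baseline and four months.

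On reporting, section 5.2 says that data completion will be summarised by arm, "along with reasons for withdrawal and any reported adverse events". Section 5.9 adds only that safety data will be described. The article nowhere separates AEs by how they came to light, limits an arm comparison to the shared visits, or gives controls a matching early contact.

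**The concern.** The same checklist is applied more often in one arm. During roughly the first two months an intervention participant may be asked about AEs up to seven times. A control participant is first asked at four months and must then remember what happened earlier. Mild or short-lived events are the ones most easily lost over such an interval. Section 5.9 names exacerbation of existing mental illness as a potential AE, and its milder, transient forms fall in this class.

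Neither participants nor research staff are blinded (section 3.1), so nothing in the design offsets the difference. Summary reports go periodically to the Independent Advisory Board (section 5.8), which may recommend halting on evidence of harm (section 5.10) and guides progression (section 5.11). A table with more AEs under the intervention could be read as a safety signal when it partly reflects how often people were asked. The same procedure could also be carried into the definitive trial.

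A second point concerns who does the asking. Section 5.9 gives AE assessment at sessions to the research assistants (RAs). Section 2.6 has the sessions "delivered over approximately six to seven weeks by trained Tobacco Dependence Advisors (TDAs") and states no RA role in them. If RAs are not present, it is unclear who records early events.

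**Working it through.** The plan has no AE rate or other safety figure to reproduce. The check is a count of scheduled elicitations, followed by an illustration on assumed rates.

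**1. Scheduled elicitations after randomisation**

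- Intervention: up to 7 sessions (section 2.6) + 2 follow-up visits (section 4) = up to 9.
- Control: 2 follow-up visits = 2.
- Ratio: 9 / 2 = 4.5. On the stated session schedule, all the excess falls before four months.

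Nine is the planned maximum. Attendance may be lower, although section 2.6 also allows sessions to be broken into shorter, more frequent contacts.

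**2. What equal true risk would look like on paper**

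Assumed inputs, none of them in the article:

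- *p*: true risk of an early non-serious AE, the same in both arms, 20–40%.
- *s*: share of such events captured at sessions, 90–100%.
- *r*: share recalled at the four-month visit, 30–70%, the same in both arms.

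An intervention participant's event is missed only if both the session and the later recall miss it. Hence:

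- Recorded in intervention = p × [1 − (1 − s)(1 − r)]
- Recorded in control = p × r
- Spurious gap = p × s × (1 − r)

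With 50 per arm (100 participants split evenly):

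| p | s | r | Intervention | Control | Gap (percentage points) | Apparent ratio |
|---|---|---|---|---|---|---|
| 0.20 | 0.9 | 0.7 | 9.7 | 7.0 | 5.4 | 1.39 |
| 0.30 | 1.0 | 0.7 | 15.0 | 10.5 | 9.0 | 1.43 |
| 0.30 | 1.0 | 0.5 | 15.0 | 7.5 | 15.0 | 2.0 |
| 0.40 | 1.0 | 0.3 | 20.0 | 6.0 | 28.0 | 3.33 |
| 0.30 | 1.0 | 1.0 | 15.0 | 15.0 | 0 | 1.0 |

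The smallest gap in the assumed range is 0.20 × 0.9 × 0.3 = 0.054 and the largest is 0.40 × 1.0 × 0.7 = 0.28. With full recall (r = 1) the gap is zero. Spontaneous reports from controls would act like a higher r and shrink it.

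**3. Restricting the comparison to shared visits**

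If the by-arm table uses only events elicited at four and seven months, the schedule is 2 against 2 and this asymmetry drops out.

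**The case against.** Several points on the other side have weight.

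- **The by-arm table is inferred.** In section 5.2 the phrase about trial arm attaches to data completion, and AEs follow in a loose clause. A by-arm split is the natural reading but not an explicit plan.
- **Little hangs on it formally.** The article plans no formal comparison, and AEs are neither a listed feasibility outcome (section 5) nor a numerical progression criterion (section 5.11). Each AE is also assessed for causality and expectedness, which helps in reading a list.
- **Symmetric measures exist.** BPRS at baseline and seven months, and PHQ-9, GAD-7, SF-12 and service use at baseline, four and seven months, are collected alike in both arms. They give an even-handed check on lasting deterioration, though they do not date short episodes in the first weeks.
- **Forms not shown.** The case report forms may already hold the date and source of each event. That would make the fix easier, but it would not change the schedule that the article states or the absence of any rule for the comparison.
- **Who assesses.** If RAs turn out not to assess AEs at sessions and nobody else does, scheduled elicitation is 2 against 2. The surveillance difference then disappears, and the problem becomes missed early events.

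A reader might infer that every by-arm AE summary from this trial must be biased against the intervention, or that a 4.5-fold contact ratio means a 4.5-fold bias. The article supports neither. A summary confined to the shared visits avoids the asymmetry, and the bias depends on how much controls forget or leave unreported, not on the contact ratio itself.

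Checking for AEs at sessions is legitimate. The fault lies in pooling what those checks find into an arm comparison.

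**Conclusion.** The point holds in a limited form. As written, section 5.9 schedules up to 9 elicitations in one arm against 2 in the other. A pooled by-arm summary may therefore overstate non-serious AEs in the intervention arm.

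The size cannot be known from the article. Under the assumed ranges it is about 5 to 28 percentage points with no true difference, and it falls to nil with complete recall by controls. Serious events are probably less affected, because they are less likely to be forgotten.

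The consequence is a potentially misleading safety picture for the Advisory Board and for planning the definitive trial. No test, sample size or numerical progression threshold is affected. The conflict over who assesses AEs at sessions is separate and needs only to be reconciled; the article does not show which section is right.

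**What to change.** 1. Record the source (session, four-month visit, seven-month visit, spontaneous report) and date of every AE.
2. Base the by-arm summary on AEs elicited with the same checklist and recall period at the four- and seven-month visits in both arms, plus serious events from any source. Ask at those visits about the whole recall period, whether or not an event was already reported at a session.
3. List session-elicited AEs separately for the intervention arm, labelled as having no control counterpart.
4. State in section 5.2 that the AE summary is by arm, if that is intended.
5. Reconcile sections 5.9 and 2.6 on who assesses and records AEs at sessions.

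The cost is one source field and date on the AE form, one split table and a few sentences. The sample size and visit schedule do not change. The downside is that the comparative table omits some real non-serious events, although these still appear in the separate listing. Source needs to be captured as events are recorded, since it may not be possible to reconstruct it reliably afterwards.

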### Aim of the study

1.1

We aim to conduct a feasibility randomised controlled trial of SCIMITAR-SA to inform the design and implementation of a future definitive trial for tobacco cessation in mental health settings of three South Asian countries.

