**At seven months follow up,** all measures from the four-month assessment and BPRS will be repeated, and an additional salivary sample will be collected to biochemically verify abstinence. We will operationalise the biochemically verified continuous abstinence from all tobacco products using the global Russell Standard of sustained and verified quitting [50]. For those who report using tobacco products on no more than 5 occasions during the cessation period (duration between the target quit date (for intervention group) or 30 days post-randomisation (for the control group) and the seven month follow up time point) at the seven-month follow-up, biochemical verification will be carried out through salivary cotinine and Anabasine testing through LC-MS (ACM Global Laboratories, UK for Bangladesh and Pakistan & Laboratory of the Department of Clinical Psychopharmacology and Neurotoxicology for India). Cotinine level <15 ng/ml will be used to identify biochemically verified abstinence), whereas those who self-report continuous abstinence but have cotinine levels above the threshold will be identified as tobacco users. Biochemically verified tobacco abstinence at seven months is included as an exploratory outcome to assess the feasibility of collecting cessation outcome data, including biochemical verification, and to inform outcome selection, measurement procedures, and sample size estimation for a future definitive trial.

Follow-up assessments at four and seven months post-randomisation will be considered on time if completed within a one-week window before or after the scheduled date. RAs will begin contacting participants one week prior to, and for up to three weeks after, each due date, making up to three phone calls per week at varying times and days to schedule the assessment. Instances of delayed follow-up will be documented and reviewed after the feasibility phase to refine procedures for the main trial. If the four-month data are missed, efforts will still be made to obtain information at the seven-month follow-up.

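### Adverse events are actively checked up to nine times in the intervention arm and twice in the control arm, so a by-arm count of non-serious events will tend to be higher in the intervention arm

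*Protocol article*

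**What the plan says.** Section 5.9 (Adverse events) sets the schedule of active enquiry: "RAs will assess AEs during counselling sessions and at four- and seven-month follow-ups using standardised checklists and case report forms". It also invites participants to report events through study contacts, and has each AE assessed for seriousness, severity, causality and expectedness.

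Section 2.4 makes the sessions specific to one arm: "Participants allocated to the intervention arm will, in addition, receive the SCIMITAR-SA intervention". Section 2.6 allows up to seven sessions, laid out as "two pre-quit sessions, a quit day session (corresponding with 30 days since enrollment) and weekly follow up to the 4-week post-quit point". It adds that "the sessions may be adapted into shorter, more frequent contacts, with duration extending beyond 6-7 weeks as needed".

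Section 4 places data collection for everyone "at baseline (after informed consent and prior to randomisation) and at four and seven months post-randomisation". On timing around each visit it says "RAs will begin contacting participants one week prior to, and for up to three weeks after, each due date".

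Section 5.2 (Statistical analysis) has data completion rates "summarised by trial arm at baseline and follow-up, along with reasons for withdrawal and any reported adverse events". It plans no formal comparisons.

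**The concern.** The number of AEs recorded depends on how often people are asked as well as on how many events occur. Here the extra questioning follows the randomised arm. It is also concentrated in the first two months, around the quit date, when two of the events named in section 5.9 (side effects of nicotine replacement and worsening of mental illness) are plausible. A short-lived event in week five would be asked about within days in one arm and only after more than two months in the other.

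A reader comparing the two columns of an AE table could then take a difference in questioning for a difference in harm. The stated aim of the trial is "to inform the design and implementation of a future definitive trial". If the definitive trial took over this AE schedule unchanged, the same tilt would come with it.

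**Working it through.** The plan states no figure on this point, so there is none to reproduce. The check counts the scheduled enquiries and then illustrates what unequal counts can do.

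**Scheduled active checks after randomisation** (sections 2.4, 2.6, 4 and 5.9)
- Sessions, intervention arm only: 2 pre-quit + 1 quit day + 4 weekly = 7.
- Visits in both arms: month four and month seven = 2.
- Intervention: up to 7 + 2 = 9. Control: 2.

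Nine is the maximum under the standard layout. Missed sessions lower it; splitting sessions into shorter contacts could raise it.

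**Timing**
- Quit day is about day 30, so the last planned session is about day 30 + 28 = day 58.
- Month four is about day 122. Contact runs from 122 − 7 = day 115 to 122 + 21 = day 143.
- The control arm's first active check therefore comes at least 115 − 58 = 57 days after the intervention arm's last planned session.

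**Illustration with equal true rates.** All values here are assumptions; none is in the document. Take 50 participants per arm and 0.10 non-serious events per participant-month. True events per arm are then 50 × 2 × 0.10 = 10 in months 0–2 and 50 × 5 × 0.10 = 25 in months 2–7. Let p be the share of events caught by the common visits (80% seen × recall), and s the share of months 0–2 events caught at sessions.
- Control total = 35p.
- Intervention total = 10 × [1 − (1 − s)(1 − p)] + 25p.
- Ratio = 1 + (2/7) × s × (1 − p)/p. The event rate cancels.

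Results:
- Central, s = 0.8, recall 0.5, p = 0.40: 8.8 + 10.0 = 18.8 versus 14.0, ratio 1.34.
- Low, s = 0.3, recall 0.8, p = 0.64: 23.5 versus 22.4, ratio 1.05.
- High, s = 0.9, recall 0.3, p = 0.24: 15.2 versus 8.4, ratio 1.81.

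The ratio exceeds 1 whenever s > 0 and p < 1; only its size depends on the assumed values.

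**Spontaneous reports.** The model leaves them out. Because both arms can make them, they act like a higher p. Holding s = 0.8 and raising p from 0.40 to 0.64 gives 1 + (2/7) × 0.8 × 0.36/0.64 = 1.13 instead of 1.34. The tilt shrinks but does not vanish.

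**A second model.** Each event is recorded at the next scheduled check with probability exp(−lag/τ). With seven sessions the simulated ratio is about 1.8, 1.27 and 1.14 for τ of 1, 3 and 6 months. With four sessions it is about 1.5, 1.2 and 1.1. With perfect recall it is 1.0.

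**Against chance.** The central excess is 18.8 − 14.0 = 4.8 events. The Poisson standard deviation of the difference is √(18.8 + 14.0) = 5.7. In a trial of this size the tilt could not be told from chance.

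**The case against.** The strongest reply is that the by-arm AE table is inferred. In section 5.2 the item clearly split by arm is data completion; AEs are attached at the end of the sentence. Section 5.9 promises only a descriptive summary. How AEs are tabulated is detail that a condensed article may leave to the full protocol or analysis plan. This stands in part: the by-arm table is a reading, though the natural one in a two-arm trial. The unequal schedule, however, is stated outright, and it is what creates the tilt.

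Second, little depends on it. AEs are not among the feasibility outcomes in section 5 or the progression criteria in section 5.11, and no test is planned. This stands in full and sets the severity. Causality assessment is a weaker defence. It classifies events already captured and cannot recover control-arm events nobody asked about, and section 3.1 says research staff are not blinded.

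Third, the number of checks is uncertain. Seven sessions is an upper limit, some may be remote, and section 5.9 gives the AE assessment to research assistants although the advisors deliver the sessions. That affects how large the imbalance is. Whoever asks, only one arm is asked.

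Fourth, a main table built only on recall at months four and seven would set aside the best-timed harm data on the intervention, in a population with cognitive difficulties. That is a fair criticism of such a remedy, and the fix below keeps the session data in view.

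A reader might also infer that the independent board could halt the trial, or judge progression, on a spurious excess. The document does not support that. Section 5.10 ties halting to new evidence of harm or benefit, and nothing says by-arm counts of non-serious AEs will be used for it. Nor does it say that the definitive trial will reuse this schedule; procedures are to be reviewed after this phase.

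**Conclusion.** The concern holds as a minor point. The schedule gives up to 9 active checks against 2, with none in the control arm before about day 115. If non-serious AEs are shown by arm and recall is imperfect, the intervention arm will tend to show more of them at equal true rates.

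The size cannot be derived from the document. The range of 1.05 to 1.81 rests on assumed capture and recall with no spontaneous reporting, so it is an illustration and not an estimate. It would be wrong to conclude that the plan inflates AE counts by a known third, or that its safety monitoring is unsound: the session checks are good practice. Serious events should be less affected. The consequence is confined to how a descriptive safety summary is read.

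**What to change.** In sections 5.9 and 5.2:

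1. Keep the session checks for participant safety.
2. Record the source of each AE: session, month-four visit, month-seven visit or spontaneous report.
3. Ask the month-four and month-seven checklists over the same recall period in both arms (since randomisation, then since month four), whether or not an event was reported earlier.
4. State that all AEs and serious AEs are reported by arm and split by source, with session-elicited non-serious events labelled as intervention arm only.
5. Base any between-arm contrast of non-serious AEs on the two common visits.

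The cost is one extra form field and some table rows, with no added visits or contacts. Asking again at month four may produce duplicate reports to reconcile with events already logged. Contrasts at the common visits will miss mild early events forgotten by then. Repeated questioning at sessions may also leave intervention participants recalling more, so the difference is reduced rather than removed.
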